#### Vaccination visit and vaccination phase

Allocated vaccine will be administered at visit day 28, after confirming that consent is valid and no temporary exclusion criterion applies. Participants will then be observed for a minimum of 45 min and asked to record solicited symptoms (listed in online supplemental tables S3, S4) daily for 7 days and unsolicited symptoms for 28 days on an electronic diary.

Follow-up visits with safety assessment and sampling will occur at day 21 and day 14 (7 and 14 days after vaccination). At 28 days after vaccination, a prechallenge visit will be conducted for blood sampling.

#### Challenge visit and challenge phase

At the challenge site, participants will be given a pre-treatment with sodium bicarbonate solution 1 min before being orally challenged with SPA (strain NVGH308) at the dose of 1–5×10^3^ CFU suspended in 30 mL of sodium bicarbonate on visit D0. Participants will fast for 90 min before and after challenge administration. They will be directly monitored for a minimum of 15 min, but they remain on site for 2 hours; if they vomit within 90 min of challenge administration, they will be withdrawn from the study and treated with antibiotics. During this observation, participants will be instructed and observed practising hand hygiene according to WHO’s guidance. They will be given access to an e-diary, where they will record solicited symptoms daily (as seen in online supplemental table S5) for 21 days, including twice-daily measured temperatures, and they may add any unsolicited symptoms and medications for 28 days.

Box 1 lists the prespecified criteria for diagnosis of paratyphoid infection: if presenting with at least one of them, participants will be considered susceptible to the disease, prompting antibiotic treatment. Recruited participants will be naïve to enteric fever, and baseline stool samples will be collected to ensure no SPA will be present prior to challenge. Since the UK is not endemic for enteric fever, and participants will not travel to endemic countries, we will assume that all SPA recovered from blood or stool culture will be the challenge strain.

Box 1Criteria for the diagnosis of paratyphoid A infectionParatyphoid A fever is diagnosed if any of the following applyA positive blood culture for SPA from 72 hours postchallenge.A positive blood culture for S. Paratyphi A within 72 hours postchallenge, with one or more signs/symptoms of paratyphoid A infection (such as recorded oral temperature ≥38.0^o^C).Persistent positive blood cultures (two or more blood cultures taken at least 4 hours apart) for S. Paratyphi A within 72 hours postchallenge.Oral temperature ≥38.0^o^C persisting for 12 hours or longer, not necessarily continuously.

During the challenge phase, participants will be asked not to take any anti-pyretics to prevent interference with the diagnostic criteria. Participants will be seen daily until day 14, and if clinically indicated, an additional review will be arranged and symptomatic medications prescribed. Participants will be reviewed for 4 days after diagnosis, if applicable. At day 14, all undiagnosed participants will also take a full course of antibiotics.

#### Follow-up visits

After the challenge phase, follow-up visits occur at days 28, 90 and 180 for safety monitoring and for sampling.

To confirm SPA clearance, all participants will bring three faecal samples at least 48 hours apart, at least 1 week after completing antibiotics. When all three samples are culture-negative for SPA, faecal clearance is confirmed. If any sample is positive, the participant will be retreated and followed up until clearance can be confirmed, to ensure no chronic carriage of SPA.

#### Laboratory testing

Samples collected for safety monitoring and microbiological endpoints will be processed and reported locally. For the primary and secondary endpoints, immunological assays to evaluate levels of anti-Vi and anti-LPS IgG, IgA and serum bactericidal assays will be validated and undertaken at an external laboratory. Exploratory endpoints will be undertaken at OVG. Blood sample collection and other samples timepoints are summarised in online supplemental table S7.

Participants will also be able to consent to transfer unused samples to the Oxford Vaccine Centre Biobank at the end of the study.

### Data management

#### Data collection

Clinical data will be collected and recorded directly into electronic case report forms using REDCap. Data entry will be quality-controlled by a second staff member. Laboratory data will be stored securely on University of Oxford’s servers. The OVG team will inspect data collection and storage throughout the study, and an external monitor will oversee monitoring.

#### Confidentiality

The study will comply with Good Clinical Practice, with the UK General Data Protection Regulation and Data Protection Act 2018, and with Sponsor security policies.

### Trial Interventions

#### Vaccine: test arm

SII-TCV(B) is an investigational bivalent conjugate vaccine against S. Typhi and Paratyphi A, manufactured by Serum Institute of India, Pune, India. A single dose of 0.5 mL contains 25 µg of the Vi polysaccharide antigen from S. Typhi conjugated to purified tetanus toxoid and 25 µg of the purified O-specific polysaccharide from S. Paratyphi A (O:2) conjugated to purified diphtheria toxoid. It is administered as a single dose, via intramuscular route. A double-blind Phase I study conducted in 60 adults in India demonstrated SII-TCV(B) to be safe and immunogenic.^18^

Single-dose vial presentation will be used. The clear, colourless to pale yellow liquid will be administered using a syringe with needle in a manner to closely match the comparator presentation.

#### Vaccine: comparator arm

Typhim Vi, a Vi-PS manufactured by Sanofi (Gentilly, France)^49^ and licensed in the UK, will be used as the comparator vaccine. Typhim Vi is indicated for active immunisation against typhoid fever via intramuscular route. A single dose of 0.5 mL contains 25 µg of the Vi-polysaccharide antigen from S. Typhi.

Prefilled single-dose syringe presentation will be used, containing this colourless solution.

#### Challenge

The original SPA strain NVGH308 was isolated in 2006 from a patient in Nepal.^50^ This strain was fully characterised and known to be sensitive to all antimicrobials routinely used to treat enteric fever. Genome sequencing has been completed at the Sanger Institute, Cambridge, UK (labelled ED199). It was manufactured to Good Manufacturing Practice standard by Novartis Vaccines and Diagnostics. The suspension vials have been stored frozen in OVG since then. Ongoing stability tests conducted by GenIbet demonstrate the viability of the challenge agent. This challenge agent has been safely used in three other trials conducted by OVG,^43 47 48^ at a combined attack rate of 66.2% (49/74, 95% CI 54.3% to 76.8%).

The challenge dose will be prepared to contain 1–5×10^3^ CFU in a 30 mL bicarbonate solution for oral ingestion, 1 min after ingestion of 120 mL of a bicarbonate buffer. Final dose is confirmed following overnight incubation in an agar plate.

#### Antibiotics

Treatment will be given to all participants, either at the time of diagnosis or at day 14 postchallenge for those who did not reach preset criteria for diagnosis. Participants will be observed taking the first dose of antibiotic; subsequent doses of antibiotics will be taken by the participant at home, with compliance checked via e-diary. Other reasons for commencing antibiotics are listed in the online supplemental box S1.

A 14-day course of ciprofloxacin (500 mg two times per day) was the first-line antibiotic course used in previous paratyphoid fever CHIMs.^43 47 48^ However, due to potential risks associated with ciprofloxacin, highlighted by the Medicines and Healthcare products Regulatory Agency (MHRA) alert in 2024,^51^ alternative strategies to reduce exposure to this antibiotic were explored. According to the British Infection Association, both azithromycin and ciprofloxacin are recommended as optimal oral options to treat enteric fever.^52^ Evidence from enteric fever CHIMs indicates that ciprofloxacin outperforms azithromycin, with quicker clearance of fever and bacteraemia, as well as quicker symptom resolution,^53^ resulting in improved antibiotic tolerability and significantly fewer instances of antimicrobial switching (unpublished data). To leverage the rapid efficacy of ciprofloxacin while mitigating potential safety concerns and reducing exposure to it, a combination regimen of 4 days of ciprofloxacin (750 mg twice daily) followed by 10 days of azithromycin (1 g on the first day, 500 mg on following days) will be the first-line treatment in this trial.

Second-line or third-line courses of antimicrobials will be offered, should a participant develop intolerance to the first line. Online supplemental box S2 lists the alternatives. In case the participant requires intravenous antibiotics, ceftriaxone will be the choice.

#### Other trial interventions

Other medications will be provided for symptomatic control of enteric fever if required, listed in the online supplemental table S8. No other trial interventions are planned.

### Sample size

The attack rate of the SPA challenge dose was estimated to be 58% on the comparator (Typhim Vi) arm, based on two previous CHIMs (22/38 participants).^43 48^ To show a VE of 70%, corresponding to an attack rate in the SII-TCV(B) arm of 17.4%, the study will need to recruit an effective sample size of 85 per arm. This is necessary to reject the null hypothesis that VE is ≤30% with 90% power at two-sided 0.05 significance level. Accounting for a dropout rate of 10% (although the attrition rate has been lower in enteric fever CHIMs), the final sample size needed is 192 volunteers.

This sample size will provide 90% power to demonstrate non-inferiority of SII-TCV(B) compared with Typhim Vi at a two-sided 0.05 significance level, assuming a 5% attrition rate. A few assumptions were used for the power calculation. First, to determine the non-inferiority of SII-TCV(B), we used WHO recommended non-inferiority margin of 0.67.^54^ Additionally, based on published data, SDs of anti-Vi IgG are 0.57 and 0.47 at log10 scale, respectively, in the Vi-PS and in the SII-TCV(B) arms, with a true geometric mean ratio (GMR) >1.2.^44^

For the primary paratyphoid endpoint (efficacy), the 30% superiority margin probably represents a stringent threshold for a VE trial using CHIM, as demonstrated in prior typhoid vaccine CHIM trials, in which VE was lower than observed in field trials,^44 55^ partly due to stringent predefined diagnostic criteria. Considering this, we conducted a sensitivity power calculation assuming the true VE is as low as 55% in the CHIM and concluded that the current sample size remains robust, providing 80% power to reject the null hypothesis that VE is ≤19% (see table 3).

**Table 3 T3:** Superiority margins at different study powers and associated vaccine efficacy

Vaccine efficacy	Superiority margin (90% power)	Superiority margin (80% power)
50%	8%	14%
55%	13%	19%
60%	19%	24%
65%	24%	30%
70%	30%	35%

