**Trial registration number:**

ISRCTN65855590.

STRENGTHS AND LIMITATIONS OF THIS STUDYThe multicentre, randomised, double-blind, controlled design of the study, with stratified allocation, will provide high-quality data.The use of a controlled human infection model will enable efficacy assessment of the first bivalent typhoid-paratyphoid A vaccine candidate, since field trials are not considered feasible due to the high cost and large sample size required.Rigorous screening procedures, including gallbladder ultrasound, prevention of chronic faecal carriage of *Salmonella* enterica Paratyphi A and enforced infection control precautions, ensure safety of the participants and their close contacts.A centralised administration of challenge associated with fully validated centralised immunogenicity assays (including anti-Vi and anti-LPS IgG and IgA for primary and secondary objectives) will provide consistent endpoints.The sample size was calculated to provide 90% power to detect a vaccine efficacy higher than 30% and to demonstrate non-inferiority of Serum Institute of India–Typhoid Conjugate Vaccine(B) compared with a plain polysaccharide typhoid vaccine as control.

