### Statistical analysis

The proportion of participants with a diagnosis of paratyphoid fever (the attack rate) in each arm with 95% CI will be presented after window for primary endpoint evaluation (after challenge phase). The VE will be estimated by calculating the difference in attack rate in the comparator and in the SII-TCV(B) arm relative to the attack rate in the comparator arm, as seen below:

 VE=100×(AR_comparator_−AR_SII-TCV(B)_)/AR_comparator_=100×(1−AR_SII-TCV(B)_/ AR_comparator_)

Where VE is the VE and AR is the attack rate. The 95% CI of VE will also be calculated—if the lower boundary of the 95% CI is at or above 30%, the vaccine will be considered efficacious to protect against paratyphoid.

The immunogenicity data will be log-transformed prior to analysis to render a normal distribution, as data are expected to be highly skewed. Values below the limit of detection will be replaced by half the value of the lower limit before transformation. Primary analysis will be conducted on a per-protocol basis for all participants who received vaccination with no critical protocol deviation. A modified intention-to-treat analysis will also be conducted as a sensitivity analysis.^56^

The geometric mean concentration of antibodies will be calculated for each arm as the antilogarithm transformation of the mean of the log10 transformed concentration, with 95% CI calculated as the antilogarithm transformation of the lower and upper limits.

For the non-inferiority primary endpoint, the GMR will be calculated as antilogarithm of the difference between the mean of the log10 transformed concentration in the SII-TCV(B) and in the comparator arms. The 95% CI will be calculated as the antilogarithm transformation of the lower and upper limits. If the lower boundary of the 95% CI of the GMR is above 0.67,^54^ this bivalent vaccine will be considered non-inferior to the comparator Vi-PS.

Secondary analysis will use the Kaplan-Meier method to conduct time-to-event analyses, such as time to positive blood culture or time to oral temperature ≥38 ºC. Participants not meeting criteria for an individual component of the primary endpoint, or who withdrew or had potential interference with vaccine effect or infection challenge, will be censored in the analysis. Sensitivity analyses by sex and age and other variables will be added.

Exploratory objectives will aim to generate new hypotheses; thus, they will be analysed descriptively.

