Although age differences between these two populations may influence vaccine-induced immune responses, particularly with respect to B-cell maturation, this effect is less pronounced for conjugate vaccines,^73^ which elicit T-cell-dependent antibody production.^74^ Pre-existing memory B-cells from prior exposure in endemic settings may further influence vaccine responses.^73^ Bridging CHIM-derived findings with age-stratified serological data from endemic populations will be essential for contextualising correlations. Notably, antibody levels conferring protection in the typhoid CHIM^44^ have been shown to be comparable to those observed in an endemic setting.^32^

The multicentre double-blind randomised controlled design with stratified allocation will provide high-quality data, with multiple centres facilitating recruitment. The sample size will provide sufficient statistical power to detect both primary endpoints. Although CHIMs may underestimate VE, as observed for TCV,^44^ likely due to stringent diagnostic criteria and large inoculum used to ensure high attack rates, the sample size maintains adequate power to detect a clinically meaningful efficacy. Based on previous studies,^18 44^ the typhoid component is expected to demonstrate non-inferiority compared with the Vi-PS vaccine. This trial will also include blood sampling to investigate correlates of protection against paratyphoid A, which remain unknown and would inform future vaccine development.

Functional antibody assays and assessment of cellular immunity may help elucidate protective responses against S. Paratyphi A infection, as observed with other enteric or Gram-negative pathogens. Antibody-dependent opsonophagocytic activity correlates with vaccine-induced protection for Vi-based typhoid vaccines^75^ and pneumococcal conjugate vaccines.^76^ Antibody-mediated complement bacterial killing serves as a correlate of protection for cholera^76^ and meningococcal vaccines^76 77^ and is associated with reduced disease severity post live typhoid vaccines^78^ and post shigella infection in a CHIM.^79^ IgA responses, mucosal immunity and memory B cells also contribute meaningfully to protection against shigellosis^80 81^ and typhoid infection.^75 81^

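### The sample size is called robust at a true VE of 55% on a 19% null, but the success rule needs a lower bound of 30%, for which power is about 60–62% (ratio-based CI)

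*Protocol article*

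**What the plan says.** The Sample size section sets up one efficacy calculation. Its starting point is this: "The attack rate of the SPA challenge dose was estimated to be 58% on the comparator (Typhim Vi) arm". The design case is a true VE of 70%, which puts the vaccine-arm attack rate at 17.4%, and 85 evaluable participants are planned in each arm. The target of the calculation is stated as: "reject the null hypothesis that VE is ≤30% with 90% power at two-sided 0.05 significance level".

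The same section then calls the 30% margin stringent, because earlier typhoid challenge trials gave lower VE than field trials. It takes 55% as a low value for the true VE in this model; it then "concluded that the current sample size remains robust, providing 80% power to reject the null hypothesis that VE is ≤19% (see table 3"). That table lists, for true VE from 50% to 70%, the margin that can be excluded with 90% and 80% power.

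Statistical analysis gives one efficacy criterion: "if the lower boundary of the 95% CI is at or above 30%, the vaccine will be considered efficacious to protect against paratyphoid".

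Two other places summarise power. The Discussion, after noting that challenge models may underestimate VE, says that "the sample size maintains adequate power to detect a clinically meaningful efficacy" and names no margin. The strengths and limitations box claims "90% power to detect a vaccine efficacy higher than 30"% and does not state the assumed true VE.

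**The concern.** A sensitivity power calculation should show how the planned test behaves when an assumption is less favourable. Here the true VE falls from 70% to 55%, but the null falls with it, from 30% to 19%. Power stays at 80% because the bar was lowered, and the trial will not be judged against that lower bar. The calculation correctly shows which margin 85 per arm can exclude at VE 55%. It does not show that the trial is robust for its own criterion.

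The 55% case is the plan's own downside scenario. The introduction and Discussion tie a positive efficacy result to licensure and prequalification. Readers, ethics reviewers and the monitoring committee should therefore be able to see the chance of meeting the stated rule in that scenario, and the text gives them a more favourable figure for a different rule.

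**Working it through.** **Inputs.** Comparator attack rate 0.58, 85 evaluable per arm, two-sided 0.05 (z = 1.96), from Sample size. Success bound VE 30%, from Statistical analysis. Vaccine-arm attack rates are 0.58 × 0.30 = 0.174 at VE 70% and 0.58 × 0.45 = 0.261 at VE 55%.

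**Step 1: reproduce the plan's figures.** The article names no formula. A pooled-variance difference formula fits:

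power = Φ[(d − m − 1.96·s0)/s1]

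Here d is the difference in attack rates, m = margin × 0.58, s0 = √(2·p̄(1−p̄)/85) with p̄ the mean attack rate, and s1 = √((p1(1−p1)+p2(1−p2))/85).

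- VE 70% against 30%: d = 0.406, m = 0.174, s0 = 0.0743, s1 = 0.0675. Φ(1.28) = 90%, as stated.
- VE 55% against 19%: d = 0.319, m = 0.1102, s0 = 0.0757, s1 = 0.0717. Φ(0.84) = 80%, as stated.
- VE 65% against 30%: 79%, in line with Table 3's 80% entry.

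A continuity-corrected unpooled difference formula also gives 85 per arm (84.01 rounded up). The stated figures are therefore right for the nulls they name.

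**Step 2: read Table 3 against the rule.** A 30% margin appears at VE 65% (80% power) and VE 70% (90% power). At VE 55% the margins are 19% and 13%. Power against 30% at VE 55% is therefore below 80% by the plan's own table.

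**Step 3: power for the 30% bound at VE 55%.**

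- Pooled difference formula: m = 0.174, so (0.319 − 0.174 − 1.96 × 0.0757)/0.0717 = −0.05, and Φ = 48%. The continuity-corrected variant gives 46%.
- Log relative risk, normal approximation: SE = √(0.739/(85 × 0.261) + 0.42/(85 × 0.58)) = 0.2045. ln(0.70/0.45) = 0.4418. Φ(0.4418/0.2045 − 1.96) = Φ(0.20) = 58%.
- Exact enumeration of all pairs of binomial counts: 60% for the log-RR interval and 62% for the ratio score test.

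**Step 4: power for the 30% bound across Table 3's range (58% attack rate, 85 per arm).**

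| True VE | Pooled difference | Exact, log-RR CI | Exact, score |
|---|---|---|---|
| 50% | 32% | 41% | 43% |
| 55% | 48% | 60% | 62% |
| 60% | 65% | 77% | 79% |
| 65% | 79% | 90% | 91% |
| 70% | 90% | 97% | 97% |

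As a plausibility check, 23/85 against 49/85 is an observed VE of 53.1% with a log-RR lower limit of 30.4%. The observed VE must therefore reach about 53%, and a true VE of 55% lies only just above that.

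**Step 5: more favourable inputs, VE 55% against 30%, exact log-RR and score.** No dropout means 192/2 = 96 per arm. The 66.2% attack rate (49/74) is the combined figure in the Challenge subsection of Trial Interventions.

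| Per arm | Comparator attack rate | Power |
|---|---|---|
| 96 | 58% | 66–69% |
| 85 | 66.2% | 70–73% |
| 96 | 66.2% | 77–79% |

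None reaches 80%.

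**The case against.** The strongest defence is that nothing is hidden or miscalculated. The sentence names its 19% null, it follows a remark that 30% is stringent, and Table 3 is presented as a table of excludable margins. A careful reader can see that 80% power against 30% needs VE 65%. This stands in full, so a reader who infers an arithmetic error would be wrong. It does not support the word robust, because the calculation did not test the criterion that decides the trial.

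A reader might also infer that the trial would miss its criterion about half the time at VE 55%. That rests on the 46–48% from absolute-difference formulas, which are inferred from the plan's numbers. The plan defines VE as a ratio and decides on its interval. Ratio-based methods put the chance of missing nearer 40% (38–40%), although the article does not name its interval method.

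At VE 60% the shortfall is marginal on ratio methods (77–79%). At the design VE of 70% those methods give 97%, so the main calculation is conservative.

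The strengths bullet is largely ordinary shorthand for rejecting VE ≤30%, and Sample size supplies the 70% assumption. To read it as claiming 90% power at every VE above 30% is too strong. The Discussion sentence can be defended for a zero margin, since power for a lower limit above 0 at VE 55% is 99%, but it does not say that this is the margin meant.

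Finally, the article does not say that missing the 30% bound would mean an ineffective vaccine. That harm depends on how others would read the result.

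**Conclusion.** The point holds as a mismatch between a stated power conclusion and the decision rule. At a true VE of 55%, with a 58% comparator attack rate and 85 evaluable per arm, power to meet the 30% rule is about 60–62% with ratio-based intervals and about 48% with the difference formula that reproduces the plan's figures. The range reflects the unnamed interval method. The conclusion that power is below 80% does not depend on that method, on dropout within the plan's allowance, or on using 66.2% in place of 58%.

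The documents do not support the inference that the trial is wrongly sized. The design case (VE 70% against 30%) reproduces and is sound.

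**What to change.** Change wording only:

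- In Sample size, keep the 19% figure, described as the margin that can be excluded with 80% power if the true VE is 55%, and withdraw the conclusion that the sample size is robust.
- Beside Table 3, state the power to meet the actual rule (lower 95% limit at least 30%) at VE 50, 55, 60, 65 and 70%, and name the interval method. With an exactly enumerated log-RR interval these are about 41, 60, 77, 90 and 97%.
- In the Discussion, say which margin the adequate-power statement refers to.
- In the strengths bullet, add that the 90% applies if the true VE is 70%.

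The cost is a less favourable stated figure. No extra participants are needed, and the decision rule stays as it is. How to describe a lower limit between 0 and 30% is a separate reporting choice and not part of this correction.
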